### Data monitoring

All the interventions applied in this study have been used in clinical practice and are not potentially harmful, so the data monitoring committee is not included in this study. Any unexpected adverse events that occurred during the intervention period will be reported to an experienced psychologist who will not be involved in this trial. To ensure the safety and effectiveness of the study, we will conduct an interim analysis when approximately 50% of the participants have completed the trial.

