### Primary and secondary outcomes

The primary outcome is the level of infertility-related stress measured by the Fertility Problem Inventory (FPI), before participants are discharged from the hospital. The secondary outcomes are the levels of anxiety and depression measured by the Hospital Anxiety and Depression Scale (HADS) before participants are discharged from the hospital.

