### Sample size

According to the pilot study, the standard deviations of FPI in the intervention group and control group were 22.91 and 29.01, respectively, and the means of FPI in the intervention group and control group were 144.29 and 159.31, respectively. We assumed that the number of patients in the intervention group was the same as that in the control group. The calculated sample size of 52 participants per group would provide 80% power with a two-tailed alpha error of 0.05. Estimating a dropout rate of approximately 5%, we will recruit at least 55 participants in each group.

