### Blinding

Medical staff will be blinded to group allocation. The researcher ([name]) who collected data will be blinded to group allocation. Other researchers and participants will be aware of the group allocation. The researcher who collected data will not be allowed to unblock the blinding.

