### Statistical methods

The qualitative data (demographic characteristics) will be statistically described by number (*n*) and percentage (%) and statistically be inferred by chi-square test. The Shapiro–Wilk test will be used to assess the normality of our data. This test is suitable for small to medium-sized samples and will help us determine whether the data follows a normal distribution. The quantitative data (scores of HADS and FPI) will be described by mean/median and standard deviation (SD)/interquartile range (IQR) and be inferred by *t* test/rank sum test. In all analyses, a *P* value of < 0.05 indicates statistical significance. To handle protocol non-adherence in our randomized controlled trial, we will use an intention-to-treat (ITT) analysis. Additionally, we will conduct a per-protocol (PP) analysis to include only those participants who fully adhered to the study protocol. By comparing ITT and PP results, we aim to understand the impact of adherence on study outcomes. All instances of non-adherence will be documented and considered during data analysis and interpretation. SPSS 21.0 (SPSS Inc., Chicago, IL) will be used for statistical analysis.

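### An interim analysis for effectiveness at about 50% completion falls under a blanket P < 0.05 rule; if the FPI is tested and can be claimed at both looks, the two-sided type I error is up to about 8.3%, not the stated 5%

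*Protocol article*

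**What the plan says.** Four statements in the protocol article bear on this point.

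- **Data monitoring** commits to one interim analysis and gives its purpose: "To ensure the safety and effectiveness of the study, we will conduct an interim analysis when approximately 50% of the participants". The timing is "when approximately 50% of the participants have completed the trial". The same section waives independent oversight: "so the data monitoring committee is not included in this study".
- **Statistical methods** sets a single threshold: "In all analyses, a *P* value of < 0.05 indicates statistical significance". It neither mentions the interim nor exempts it.
- **Sample size** states the error rate the trial claims: "The calculated sample size of 52 participants per group would provide 80% power with a two-tailed alpha error of 0.05". It makes no allowance for a second look.
- **Primary and secondary outcomes** names one primary outcome: "The primary outcome is the level of infertility-related stress measured by the Fertility Problem Inventory (FPI), before participants are discharged from the hospital".

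The article does not name the outcome examined at the interim. It does not say whether the trial may stop or claim success at that point, or who performs or sees the analysis. On access, Data collection and management limits the dataset to two researchers. Blinding keeps the data collector and medical staff blinded and adds: "Other researchers and participants will be aware of the group allocation".

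**The concern.** Effectiveness is a stated purpose of the interim, and the threshold for all analyses is 0.05. Read together, these sentences permit a between-group test of the FPI at half the data and another at the end, each judged at 0.05. Two chances at an unadjusted 5% level do not give a 5% error rate overall, so the alpha in Sample size would not be the trial's alpha. A positive FPI result would then carry more false-positive risk than the protocol says.

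Stopping boundaries are often left to a full protocol or an analysis plan, and their absence from an article is not the complaint. The complaint is that the article itself fixes the level for every analysis. A separate plan with adjusted limits would contradict it, so the text has to change in either case.

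There is also a possible secondary risk. With no monitoring committee, the midpoint difference could reach researchers who know the allocation while they are still enrolling participants and delivering the intervention.

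**Working it through.** **1. The plan's own sample size.** Inputs from Sample size: means 144.29 and 159.31, SDs 22.91 and 29.01, two-sided alpha 0.05, power 80%, equal groups.

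- Difference: 159.31 − 144.29 = 15.02.
- Root-mean-square SD: √[(22.91² + 29.01²)/2] = 26.14.
- Normal approximation: n = 2 × [26.14 × (1.960 + 0.842)/15.02]² = 47.5, so 48 per group. The t test needs 49.
- Rank sum test, using its efficiency of 0.955 under normality: 49/0.955 = 51.3, so 52 per group. This matches the stated figure, and Statistical methods names the rank sum test as one option.
- Dropout: 52/0.95 = 54.7, so 55, as stated.

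The stated 52 therefore corresponds to a single final test at 0.05. At 52 per group the power is 83.4% (normal approximation) or 82.7% (t test).

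**2. Type I error with two looks at 0.05.** The information fraction is about 0.5, that is 26 of 52 per group. Under no difference, the interim and final statistics Z₁ and Z₂ are bivariate normal with correlation √0.5 = 0.707. If significance at either look counts as success,

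type I error = 1 − P(|Z₁| < 1.96 and |Z₂| < 1.96).

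| Information fraction at the interim | Two-sided type I error |
|---|---|
| 0.40 | 8.63% |
| 0.50 | 8.31% |
| 0.60 | 7.96% |

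A simulation of the t statistic at 26 and 52 per group, with the protocol's SDs and no difference in means (400,000 trials), gave 8.33%. The excess at fraction 0.5 is 8.31 − 5.00 = 3.31 percentage points, or 8.31/5 = 1.66 times the stated level.

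**3. If the interim supports no efficacy claim.** Only the final test can reject, so the error is 5%. The range across readings of the text is therefore 5% to about 8.3%.

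**4. Limits that restore 5% for two equally spaced looks.**

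| Rule | Interim two-sided P | Final two-sided P | Overall error |
|---|---|---|---|
| O'Brien-Fleming (\|Z\| > 2.797, then 1.977) | 0.0052 | 0.0480 | 5.0% |
| Pocock (\|Z\| > 2.178 at both) | 0.0294 | 0.0294 | 5.0% |
| P < 0.001, then P < 0.05 | 0.001 | 0.05 | 5.02% |

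**5. Power cost of the O'Brien-Fleming final limit.** At 52 per group the expected final Z is 15.02/(26.14 × √(2/52)) = 2.93. The power of the final test is Φ(2.93 − 1.96) = 83.4% at 0.05 and Φ(2.93 − 1.977) = 83.0% at 0.0480.

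**The case against.** The strongest objection is that the premise is inferred. Data monitoring speaks of the effectiveness of the study, not of the therapy, and the sentence follows directly on adverse-event reporting. No sentence says that a P value for the FPI will be computed at the interim, or that a significant one would end the trial. The blanket 0.05 rule sits in a paragraph on chi-square, t and rank sum tests that never mentions the interim.

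This stands in part. A reader might infer that the trial's type I error simply is 8.3%. The article does not support that, because it states neither the interim comparison nor its consequence. The objection does not remove the point, however. Effectiveness is a declared purpose of the look, the threshold is declared for all analyses, and nothing in the article excludes the unadjusted reading.

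Two further inferences go beyond the text:

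- **Multiplicity across scales.** A reader might extend the calculation to the FPI and both HADS subscales at both looks and quote a much larger error. Most of that increase would come from testing several outcomes, which happens with or without an interim. It would also need a correlation the article does not give, and the article names one primary outcome.
- **An unblinded team taking the look.** A reader might conclude that researchers who know the allocation will run the interim and influence the second half. The article does not say who performs or sees it. Participants know their own allocation regardless. This is a possible risk only.

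**Conclusion.** The point holds in conditional form: the text is wrong as written, because it combines an interim for effectiveness, an unadjusted 0.05 for every analysis and a claimed overall alpha of 0.05.

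The two-sided type I error on the FPI is up to about 8.3% on two assumptions: that the FPI is compared between groups at the interim, and that significance at either look can count as success. The imprecise timing barely matters (8.0% to 8.6% for fractions 0.6 to 0.4). If the interim makes no efficacy claim, the error stays at 5%. The arithmetic is firm. Which case applies cannot be settled from the article.

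**What to change.** Choose one of two changes.

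1. **No efficacy look (simplest).** State in Data monitoring that the interim covers only adverse events, recruitment and data completeness, with no between-group comparison of FPI or HADS and no stopping for effectiveness. The final test keeps 0.05.
2. **Keep an efficacy look.** State that the interim and final FPI tests are exempt from the blanket rule in Statistical methods and use O'Brien-Fleming limits: two-sided P < 0.0052 at 50% and P < 0.0480 at the end. Say who performs the analysis and who sees the result.

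Trial status has recruitment running from June to December 2023, so the look may already have been taken. In that case the protocol must not be reworded to describe something that did not happen. The report should say what was compared, by whom and at what threshold. If the FPI was tested, the final level must be set accordingly. P < 0.0480 is adequate only if the interim limit actually applied was no looser than 0.0052. If success could have been claimed at 0.05, that look alone used the full 5%, and the report should state the inflated error.

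Cost: about one sentence in each of the two sections and no extra participants. The first option gives up a possible early stop in a trial with about six months of recruitment. The second makes the final threshold slightly stricter, which lowers the power of the final test from 83.4% to 83.0% under the protocol's assumptions.

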### Ethics approval and consent to participate

This study was approved by the ethics committee of West China Second University Hospital (No. 2022283). All amendments proposed by the ethics committee were sent to the ethics committee before study approval. One researcher ([name]) will obtain the informed consent from all participants. All data provided to our study will be kept in strict confidence, and none of the participants’ identifying information will be reported. All procedures in this study will be conducted in accordance with the ethical standards of the responsible committee on human study and with the Helsinki Declaration and later revision.

### Dissemination plans

The results of this study will be published in a scientific journal. The selection of the authorship is based on several considerations, including the following items: contribute to the study design, data collection, data analysis, data interpretation, manuscript drafting, and manuscript revising. Scientific presentations for researchers, healthcare practitioners, and/or the public present another forum for dissemination of our results.

## Discussion

Infertility has several health and social consequences, including poor physical and mental well-being, disease stigma, violence from family, marriage breakdown, and economic pressure [22]. Infertility affects the mental well-being of more women than men. Infertile women had higher levels of infertility-related stress, anxiety, and depression than infertile men [5, 8]. Infertile women coping with stress might benefit by disclosing their experience of infertility, so mental care needs to encourage the expression and sharing of emotions during treatment [11, 12]. Expressive art therapy (EAT) has been incorporated into various programs as an element of both foundational and supportive treatment. EAT combines physical and psychological nonmainstream methods, including dance/movement, drawing, painting, sculpting, music, writing, sound, and improvisation [13]. This diversity of intervention methods caters to the varied needs of patients, providing a more comprehensive and adaptable treatment framework. Moreover, this study underscores the significance of cultural sensitivity among expressive art therapists, which is instrumental in effectively engaging patients from Chinese cultural backgrounds, thus enhancing the efficacy of interventions.

This study will employ a randomized controlled trial design, bolstering internal validity. Randomly assigning participants to either the intervention or control groups serves to mitigate the impact of selection bias, heightening the reliability of our results [23]. Additionally, the study will use robust measurement tools such as the Hospital Anxiety and Depression Scale (HADS) and the Fertility Problem Inventory (FPI) for assessing anxiety, depression, and infertility-related stress. These instruments have demonstrated validity and reliability in prior research, ensuring the robustness and comparability of our findings [18, 19, 21].

Thus, our study will verify the effectiveness of EAT for anxiety, depression, and infertility-related stress in infertile women. If our hypothesis is supported, this study will provide valuable information on mental health care strategies for infertile women and inform the design of future research and programs focused on infertility-related stress interventions.

## Trial status

The study protocol was version 1.0 on the date of March 2023 for ethical review in the West China Second University Hospital. Recruitment commenced in June 2023. Recruitments will be completed in December 2023.

## Data Availability

Data will be available from the corresponding author upon request once they have been collected.

## Abbreviations

HADS: Hospital Anxiety and Depression Scale
FPI: Fertility Problem Inventory
EAT: Expressive art therapy
SPIRIT: Standard Protocol Items: Recommendations for Interventional Trials
QR code: Quick Response Code
SD: Standard deviation
IQR: Interquartile range
